## Appendix 11: TNM Staging

**Table 1. Definitions for T, N, M**

### Primary Tumor (T)

- TX Primary tumor cannot be assessed
- T0 No evidence of primary tumor
- Tis Carcinoma in situ: intraepithelial or invasion of lamina propria
- T1 Tumor invades submucosa
- T2 Tumor invades muscularis propria
- T3 Tumor invades through the muscularis propria into the pericolorectal tissues
- T4a Tumor penetrates to the surface of the visceral peritoneum
- T4b Tumor directly invades or is adherent to other organs or structures

### Regional Lymph Nodes (N)

- NX Regional lymph nodes cannot be assessed
- N0 No regional lymph node metastasis
- N1 Metastasis in 1-3 regional lymph nodes
- N1a Metastasis in one regional lymph node
- N1b Metastasis in 2-3 regional lymph nodes
- N1c Tumor deposit(s) in the subserosa, mesentery, or nonperitonealized pericolic or perirectal tissues without regional nodal metastasis
- N2 Metastasis in four or more regional lymph nodes
- N2a Metastasis in 4-6 regional lymph nodes
- N2b Metastasis in seven or more regional lymph nodes

### Distant Metastasis (M)

- M0 No distant metastasis
- M1 Distant metastasis
- M1a Metastasis confined to one organ or site (e.g., liver, lung, ovary, nonregional node)
- M1b Metastases in more than one organ/site or the peritoneum

**Table 2. Anatomic Stage/Prognostic Groups**

| Stage | T      | N      | M   | Dukes* | MAC*  |
|-------|--------|--------|-----|--------|-------|
| 0     | Tis    | N0     | M0  | -      | -     |
| I     | T1     | N0     | M0  | A      | A     |
|       | T2     | N0     | M0  | A      | B1    |
| IIA   | T3     | N0     | M0  | B      | B2    |
| IIB   | T4a    | N0     | M0  | B      | B2    |
| IIC   | T4b    | N0     | M0  | B      | B3    |
| IIIA  | T1-T2  | N1/N1c | M0  | C      | C1    |
|       | T1     | N2a    | M0  | C      | C1    |
| IIIB  | T3-T4a | N1/N1c | M0  | C      | C2    |
|       | T2-T3  | N2a    | M0  | C      | C1/C2 |
|       | T1-T2  | N2b    | M0  | C      | C1    |
| IIIC  | T4a    | N2a    | M0  | C      | C2    |
|       | T3-T4a | N2b    | M0  | C      | C2    |
|       | T4b    | N1-N2  | M0  | C      | C3    |
| IVA   | Any T  | Any N  | M1a | -      | -     |
| IVB   | Any T  | Any N  | M1b | -      | -     |

**Note:** cTNM is the clinical classification, pTNM is the pathologic classification. The y prefix is used for those cancers that are classified after neoadjuvant pretreatment (e.g., ypTNM). Patients who have a complete pathologic response are ypT0N0cM0 that may be similar to Stage Group 0 or I. The r prefix is to be used for those cancers that have recurred after a disease-free interval (rTNM).

\*Dukes B is a composite of better (T3 N0 M0) and worse (T4 N0 M0) prognostic groups, as is Dukes C (Any TN1 M0 and Any T N2 M0). MAC is the modified Astler-Coller classification

a Tis includes cancer cells confined within the glandular basement membrane (intraepithelial) or mucosal lamina propria (intramucosal) with no extension through the muscularis mucosae into the submucosa.

b Direct invasion in T4 includes invasion of other organs or other segments of the colorectum as a result of direct extension through the serosa, as confirmed on microscopic examination (for example,

invasion of the sigmoid colon by a carcinoma of the cecum) or, for cancers in a retroperitoneal or subperitoneal location, direct invasion of other organs or structures by virtue of extension beyond the muscularis propria (i.e., respectively, a tumor on the posterior wall of the descending colon invading the left kidney or lateral abdominal wall; or a mid or distal rectal cancer with invasion of the prostate, seminal vesicles, cervix, or vagina).

c Tumor that is adherent to other organs or structures, grossly, is classified cT4b. However, if no tumor is present in the adhesion, microscopically, the classification should be pT1-4a depending on the anatomical depth of wall invasion. The V and L classifications should be used to identify the presence or absence of vascular or lymphatic invasion, whereas the PN site-specific factor should be used for perineural invasion.

**Laparoscopy-Assisted Surgery for Carcinoma of the Low  
Rectum: A Prospective, Multi-Center, Randomized, Open-  
Label, Parallel-Group, Non-Inferiority Clinical Trial  
(LASRE Trial)**

## List of abbreviations and definition of terms

| Abbreviations | Definition of terms                        |
|---------------|--------------------------------------------|
| APR    | Abdominoperineal resection                 |
| ASA    | American Society of Anesthesiologists      |
| BMI    | Body mass index                            |
| CI     | Confidence interval                        |
| CRMs   | Circumferential resection margins          |
| DFS    | Disease-free survival                      |
| DRMs   | Distal resection margins                   |
| ECOG   | Eastern Cooperative Oncology Group         |
| FSFI   | Female sexual function index               |
| HR     | Hazard ratio                               |
| IIEF-5 | International Index of Erectile Function-5 |
| IMA    | Inferior mesenteric artery                 |
| I-PSS  | International prostate symptom score       |
| IQR    | Interquartile range                        |
| ISR    | Intersphincteric resection                 |
| ITT    | Intention to treat                         |
| LAR    | low anterior resection                     |
| Max    | Maximum                                    |
| Min    | Minimum                                    |
| mITT   | Modified intention-to-treat                |
| OS     | Overall survival                           |
| pCR    | Pathological complete response             |
| PPS    | Per-protocol set                           |
| PRM    | Proximal resection margin                  |
| QoL    | Quality of life                            |
| SAE    | Serious adverse events                     |
| SDs    | Standard deviations                        |
| SS     | Safety set                                 |
| TME    | Total mesorectal excision                  |
| ULAR   | Ultralow anterior resection                |

# 1 Background

According to the World Health Organization (WHO) report in 2005, there are 400,000 new colorectal cancer patients annually in China. Colorectal cancer has become the third-leading cause of cancer-related death in Chinese patients, with an annual mortality rate of 16.83 per 100,000. Low and mid rectal cancers account for approximately 70% to 80% of rectal cancers in China. Total mesorectal excision (TME) is still the primary treatment for rectal cancer. Recent studies have shown that laparoscopy-assisted resection is safe for treating low rectal cancer. It has the advantages of minimally invasive procedures: faster postoperative recovery, less pain, shorter hospital stay, and long-term efficacy comparable to open surgery.

Randomized control trials with large samples were launched to investigate laparoscopic and open surgery for colorectal cancer in European and North American countries, including the CLASSIC trial, the COLOR trial, and the COST study. These studies compared the completeness of tumor resection, long-term efficacy, and patient's Quality of life (QoL) between the two surgical approaches. The results showed that laparoscopic resection did not increase complications or operative mortality compared with open resection in treating rectal cancer. The two surgeries were comparable in the distance and negative rate of pathological resection margins (proximal, distal, and circumferential) and the number of dissected lymph nodes. Many meta-analyses have found no significant differences between the two surgical approaches in local recurrence rate, distant metastasis rate, or disease-free survival (DFS) rate.

Recent studies have also shown that laparoscopic total mesorectal excision (TME) for rectal cancer after preoperative chemoradiotherapy is safe without increasing the incidence of surgery-related complications or mortality. Moreover, with the accumulation of surgical experience and skills, the conversion rate from laparoscopic surgery to open surgery gradually decreases. However, the interpretation of these findings needs to be further discussed.

The 2013 National Comprehensive Cancer Network (NCCN) Guidelines v.4 for colon cancer recommended laparoscopic surgery to treat colon cancer, which should be performed by experienced surgeons. However, limited by the lack of data from randomized controlled studies with large samples, the 2013 NCCN Guidelines v.4 only recommended laparoscopic radical resection of rectal cancer for clinical research.

TME has been recognized as the "gold standard" for radical resection of mid and low rectal cancer. Due to the unique anatomical characteristics of low rectal cancer (within 5 cm from the dentate line), open surgery cannot avoid the disadvantage of the limited exposure to the pelvic floor. In contrast, the 30° lens of the laparoscope has advantages in visualizing the deep pelvic structure; in patients with low rectal cancer, the pelvic operating field can be visualized to ease the separation and nudization of the lower end of the rectum. The benefits of neoadjuvant chemoradiotherapy for patients with resectable cT3/T4aN0 M0 or cT1-4aN1-2M0 low-rectal cancer have not been fully confirmed. In these patients, laparoscopic surgery's safety and long-term efficacy still need to be evaluated and compared with open surgery.

ClinicalTrials.gov, an international clinical trial registry platform, reveals seven ongoing large-scale prospective randomized controlled trials concerning laparoscopic resection for rectal cancer across the world (Table 1). However, there is no randomized controlled trial of laparoscopic surgery, especially addressing low rectal cancer.

Thus, we designed this trial to assess the perioperative safety and long-term efficacy of laparoscopic surgery for low rectal cancer compared with open surgery. The findings from this study will provide high-level evidence for clinical decision-making for surgical treatment in patients with low rectal cancer.

## **2 Objective**

To evaluate the perioperative safety and long-term efficacy of laparoscopy-assisted surgery for low rectal cancer compared to open surgery.

## **3 Study design**

This study is a prospective, multicenter, randomized, open-label, parallel-group, non-inferiority clinical trial.

## **4 Inclusion criteria**

- 1) Aged 18-75 years;

2) Pathological diagnosis of rectal adenocarcinoma (including highly and moderately differentiated tubular adenocarcinoma, papillary adenocarcinoma, poorly differentiated tubular adenocarcinoma, mucinous adenocarcinoma, and signet-ring cell carcinoma);

3) The lower margin of the tumor is < 5 cm from the dentate line at the time of initial diagnosis by rigid proctoscopy;

4) cT1-3N0-2M0 or cT4aN0-2M0 adenocarcinoma after neoadjuvant chemoradiotherapy. Patients with pelvic lateral lymph nodes are ineligible;

5) Primary tumor < 6 cm in size;

6) No other concurrent primary cancers;

7) Adequate function of main organs, allowing surgical treatment;

8) Patients and their family members can understand the study plan, are willing to participate, and agree to give written informed consent.

## **5 Exclusion criteria**

1) Aged < 18 or > 75 years;

2) Concurrent or previous malignancies within five years;

3) Need for emergency surgery due to intestinal obstruction, intestinal perforation, intestinal hemorrhage, etc. ;

4) Previous history of colorectal surgery that might affect the reconstruction of the digestive tract;

5) Need to remove other organs in addition to the rectum;

6) ASA classification IV or V;

7) Current pregnancy or lactation:

- Women of childbearing age with a positive pregnancy test at baseline or who have not taken a pregnancy test; postmenopausal women must be at least 12 months postmenopausal;

- Sexually active men and women (of reproductive age) who are unwilling to take contraceptive measures during the study period;

8) Severe mental illness;

9) Inability to tolerate surgery due to severe emphysema, interstitial pneumonia, ischemic heart disease, etc.;

10) Continuous systemic steroid therapy within the last month;

11) Contraindications to laparoscopic surgery;

12) Patients and their family members cannot understand the conditions and objectives of this study.

## **6 Surgical treatment plan**

### **6.1 Open surgery**

This surgery includes standard TME and dissection of the No. 253 lymph nodes. The inferior mesenteric artery (IMA) is ligated either from its base directly or after the branching of the left colon artery. The distal resection margin (DRM) of the rectum is at least 1-2 cm away from the tumor. The surgical method is chosen as follows:

1) Transabdominal low anterior resection (LAR) or ultralow anterior resection (ULAR) may be chosen if the lower margin of the tumor is  $\geq 2$  cm from the proximal side of the anorectal ring;

2) In cT1 and T2 patients, as well as T3 patients whose external anal sphincters are not invaded by the tumor (including patients who have undergone neoadjuvant therapy), intersphincteric resection (ISR) through either the transpelvic approach or transanal approach may be chosen when the lower margin of tumor is  $< 2$  cm from the proximal end of the anorectal ring;

3) cT1 to T3 tumors that are  $\geq 5$  cm from the anal verge are confined to the intestinal wall within a depth  $\leq 3$  cm and affect 1/2 of the circumferential wall of the rectum without invading the bladder, prostate, or vagina can be treated with ULAR via a pull-through procedure;

4) Abdominoperineal resection (APR) can be performed in patients with external anal sphincter invasion;

5) Extralevator abdominoperineal excision (ELAPE) can be performed via the pelvic approach in patients with levator ani muscle invasion;

For patients receiving sphincter preservation or partial sphincter preservation, loop transverse colostomy or ileostomy is recommended.

### **6.2 Laparoscopic surgery**

The indications of laparoscopic operation are the same as those of open operation. The operation follows the principle of TME and includes the dissection of the No. 253 lymph nodes. The IMA is ligated either from its base directly or after the branching of the left colon artery.

The rectal DRM should be at least 1 to 2 cm away from the tumor. The principles for selecting the intestinal segmental resection and/or reconstruction methods are the same as in "**6.1 Open surgery**". Prophylactic transverse colostomy or ileostomy is recommended for patients who undergo anal sphincter-preserving surgery.

## **7 Study endpoints**

### **7.1 Primary outcome measure**

3-year DFS rate (final calculation is done 3 years after the last participant is enrolled)

### **7.2 Secondary outcome measures**

#### ■ Pathologic outcomes

Pathologic outcomes are defined as TME quality, negative CRM and negative DRM, length of proximal resection margin (PRM), length of DRM, and the number of retrieved lymph nodes.

#### ■ 30-day postoperative complications

#### ■ 30-day postoperative mortality

#### ■ 3-year and 5-year OS rates (calculated 3 and 5 years after the last participant is enrolled)

#### ■ Locoregional recurrence rate

### **7.3 Other pre-specified outcome measures**

#### ■ Operative outcomes:

1) Operation time (min)

2) Estimated blood loss (ml)

3) Conversion to open surgery (only applicable to the laparoscopic resection group)

4) Events of intraoperative complications

#### ■ Postoperative recovery outcomes

1) Time to first flatus (h)

- 2) Time to the first defecation (h)
- 3) Time to first liquid food (h)
- 4) Time to normal diet (h)
- 5) Duration of analgesic use (h)
- 6) Length of postoperative hospital stay (d)

## ■ The quality of life (QoL)

☐ Quality of life (QoL) assessment: the EORTC QLQ C30 and EORTC QLQ CR29 scores

☐ Bladder function assessment:

- The residual urine volume (1st measurement: after the urethral catheter is removed on the fifth day after the operation, the residual urine volume in the bladder is determined by B-ultrasound after the patient urinates as much as possible for the first time)

- I-PSS

☐ Patient self-reported sexual function

Patient self-reported sexual function as assessed by the International Index of Erectile Function (IIEF-5) Female Sexual Function Index (FSFI) for male and female sexual function.

## 8 Statistical analyses

### 8.1 Sample size estimation

The sample size was estimated using a log-rank test based on a 3-year DFS with a noninferiority margin of 10%. At the time of this trial design, a noninferiority margin of 10% was determined to be clinically acceptable. Considering distinct prognoses in patients with stage I versus II/III disease, the sample size was calculated separately. Assumptions for the 3-year DFS rate in the open surgery group were 94.3% and 75.2% for clinical stage I and II/III diseases, respectively, with 359 patients with stage I disease (laparoscopic 240, open 119), 609 patients with stage II/III disease (laparoscopic 406, open 203), and a total of 968 patients (laparoscopic 646, open 322) were required to provide an 80% power with a one-sided  $\alpha$  of 2.5%. One thousand sixty-five patients were aimed to enroll to allow for exclusions after

randomization to maintain the required statistical power. All calculations allowed for a 20% dropout. The planned and follow-up period were three years and five years, respectively.

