**Table 5. Quality of TME and Pathologic Outcomes**

| Characteristics                       | Laparoscopic Surgery Group (n=XXX) | Open Surgery Group (n=XXX) | Difference,% (95% CI) | P value |
|----------------------------------------------|-------------------------------------------|-----------------------------------|------------------------------|----------------|
| Quality of TME, n (%)                 |                                           |                                   |                              | X.XX
X      |
| Complete                                     | XXX(XX.X)                                 | XXX(XX.X)                         | XX (XX.X–XX.X)               |                |
| Near-complete                                | XXX(XX.X)                                 | XXX(XX.X)                         | XX (XX.X–XX.X)               |                |
| Incomplete                                   | XXX(XX.X)                                 | XXX(XX.X)                         | XX (XX.X–XX.X)               |                |
| Quality of TME for stage I, n (%)     |                                           |                                   |                              | X.XXX          |
| Complete                                     | XXX(XX.X)                                 | XXX(XX.X)                         | XX (XX.X–XX.X)               |                |
| Near-complete                                | XXX(XX.X)                                 | XXX(XX.X)                         | XX (XX.X–XX.X)               |                |
| Incomplete                                   | XXX(XX.X)                                 | XXX(XX.X)                         | XX (XX.X– XX.X)              |                |
| Quality of TME or stage II/III, n (%) |                                           |                                   |                              | X.XXX          |
| Complete                                     | XXX(XX.X)                                 | XXX(XX.X)                         | XX (XX.X–XX.X)               |                |
| Near-complete                                | XXX(XX.X)                                 | XXX(XX.X)                         | XX (XX.X–XX.X)               |                |

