**Table 7. The DFS (mon) for Laparoscopic Surgery vs Open Surgery within 3 Years after Surgery (mITT)**

|                    | Laparoscopic Surgery Group | Open Surgery Group | P value |
|--------------------|-----------------------------------|---------------------------|-----------------------|
| N           | XXX                               | XXX                       | X.XXX                 |
| Censored(%) | XX(XX.X)                          | XX(XX.X)                  |                       |
| Events(%)   | XX(XX.X)                          | XX(XX.X)                  |                       |
| 25%(95%CI)  | XX.X (XX.X~XX.X)                  | XX.X (XX.X~XX.X)          |                       |
| 50%(95%CI)  | XX.X (XX.X~XX.X)                  | XX.X (XX.X~XX.X)          |                       |
| 75%(95%CI)  | XX.X (XX.X~XX.X)                  | XX.X (XX.X~XX.X)          |                       |

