**Table 9. Cox Regression Model Analysis of DFS (mITT)**

|               |                                      | DF | HR | 95%CIL | 95%CIU | P value |
|---------------|--------------------------------------|-----------|-----------|---------------|---------------|----------------|
| Group  | Laparoscopic Surgery vs Open Surgery | X         | X.XX      | X.XX          | X.XX          | X.XXX          |
| Center | Center 1 vs Center X                 | X         | X.XX      | X.XX          | X.XX          | X.XXX          |
|               | Center 2 vs Center X                 | X         | X.XX      | X.XX          | X.XX          | X.XXX          |
|               | Center...vs Center X                 | X         | X.XX      | X.XX          | X.XX          | X.XXX          |
| XXX    |                                      | X         | X.XX      | X.XX          | X.XX          | X.XXX          |

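### The trial is sized as two stage-specific noninferiority tests, but the SAP lists only one overall DFS comparison, so the stated 80% power describes tests that are not listed and an overall claim can succeed with stage II/III truly 10 points worse

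*Combined protocol and SAP*

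**What the plan says.** **Sizing.** SAP 8.1 (repeated in protocol section 5 and the protocol summary) works "based on a 3-year DFS with a noninferiority margin of 10" per cent and gives its reason for splitting the calculation: "Considering distinct prognoses in patients with stage I versus II/III disease, the sample size was calculated separately". The assumed 3-year DFS in the open arm is "94.3% and 75.2% for clinical stage I and II/III diseases, respectively". The results are "359 patients with stage I disease (laparoscopic 240, open 119") and "609 patients with stage II/III disease (laparoscopic 406, open 203"), added to 968. Both carry 80% power at one-sided 2.5%. Protocol 9.1 also uses clinical stage as a minimization factor.

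**Analysis.** SAP 8.3.3 (and protocol 12.2) compares the two arms by log-rank test and a Cox hazard ratio with a one-sided 95% confidence interval. It then draws one conclusion from noninferiority criteria that it does not spell out. Stage is not mentioned.

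**Table shells.** Table 7, "The DFS (mon) for Laparoscopic Surgery vs Open Surgery within 3 Years after Surgery (mITT"), has one column per arm and no stage rows. Table 8 is the same for the per-protocol set, and Figures 1 and 2 follow suit. Table 9, "Cox Regression Model Analysis of DFS (mITT"), has rows for group, center and one unnamed covariate marked XXX. Table 5, by contrast, splits the pathology results by stage, starting with "Quality of TME for stage I, n".

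**The concern.** Stage drove the size of the trial for the primary endpoint, yet it is carried into the analysis only for secondary pathology outcomes. Two consequences follow.

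First, a reader takes the stated 80% to be the power of the primary analysis. It belongs to two tests that the SAP does not list.

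Second, a 10-point margin applied to everyone together lets the lower-risk stage I patients offset a deficit in stage II/III. The protocol background names cT3/T4a or node-positive disease as the setting where laparoscopic safety and long-term efficacy remain to be shown. A successful overall result would naturally be read as covering those patients, and the plan offers nothing that would show whether it does.

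**Working it through.** **Inputs (SAP 8.1).** Open-arm 3-year DFS 0.943 (stage I) and 0.752 (stage II/III); margin 0.10; N 240 + 119 and 406 + 203; one-sided 2.5%; 80% power; 20% dropout. From SAP 7.1: analysis 3 years after the last enrolment. Assumed: exponential DFS and 3 years of uniform accrual (the plan's wording on periods is incomplete).

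**1. Are 359 and 609 sizes for two separate tests?**
- Margin as a hazard ratio, ln(S − 0.10)/ln(S): stage I ln(0.843)/ln(0.943) = 2.91; stage II/III ln(0.652)/ln(0.752) = 1.50.
- Events (Schoenfeld, 2:1 allocation), (1.96 + 0.8416)² / [(2/9)(ln HR)²]: 7.849/(0.2222 × 1.141) = 30.96, so 31; 7.849/(0.2222 × 0.1648) = 214.4, so 215.
- Event probability, with 3λ = −ln(S), 1 − (e^(−3λ) − e^(−6λ))/(3λ): 0.0841 and 0.3457.
- N = events/probability: 369 and 622, each within 3% of 359 and 609.

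This match has no dropout inflation. Dividing by 0.8 gives 462 and 778, and reading the periods as 3 + 5 years with that division gives 325 and 587; neither fits both figures. So the figures behave as two stage-specific sizes, but how dropout entered is unclear.

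**2. Power of the overall comparison if the arms are truly equal.** All calculations use 968, not the 1065 enrolment target.
- Stage shares: 359/968 = 0.371 and 609/968 = 0.629.
- Overall open DFS: (359 × 0.943 + 609 × 0.752)/968 = 0.8228.
- SE of the difference: √[0.8228 × 0.1772 × (1/646 + 1/322)] = 0.0260; with 20% lost, 0.0291.
- Power Φ(0.10/SE − 1.96): 97% and 93%.

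**3. Overall success when stage II/III is truly 10 points worse.** The SAP gives no HR margin, so this uses the 3-year difference against −10 points.
- Stage I equal: overall deficit 0.629 × 10 = 6.29 points; laparoscopic DFS 0.7599.
- SE: √[0.7599 × 0.2401/646 + 0.8228 × 0.1772/322] = 0.0271; with 20% lost, 0.0303.
- P(success) = Φ((0.10 − 0.0629)/SE − c), with c = 1.96 or 1.645.

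| True stage I deficit | Overall deficit | One-sided 2.5%: no loss / 20% loss |
|---|---|---|
| 0 points | 6.29 | 28% / 23% |
| 3 points | 7.40 | 16% / 13% |
| 5 points | 8.15 | 10% / 9% |

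- With the one-sided 95% interval that the SAP names (c = 1.645) and stage I equal: 39% / 34%.
- Stage I share varied (stage I equal, 20% loss, c = 1.96): at 20%, deficit 8.0, SE 0.0323, 9%; at 50%, deficit 5.0, SE 0.0285, 42%.
- With stage I equal, the overall deficit reaches 10 points only when stage II/III is 10/0.629 = 15.9 points worse.

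**4. Does the answer depend on the risk-difference rule?** In simulation (4,000 trials per scenario, stage I equal), the Kaplan-Meier difference gave 28% / 24% at one-sided 2.5%. An unadjusted Cox model also gave 28% / 24%, against a derived overall HR margin of ln(0.7228)/ln(0.8228) = 1.66. A stage-stratified Cox model against the same 1.66 gave 21% / 18%.

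**5. Power of stage-specific tests at one-sided 2.5%, arms equal.**

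| | Log-rank, no loss / 20% loss | Risk difference, no loss / 20% loss |
|---|---|---|
| Stage II/III | 79% / 70% | 77% (SE 0.0371) / 67% (SE 0.0415) |
| Stage I | 79% / 70% | 97% (SE 0.0260) / 93% (SE 0.0291) |

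The stage I normal approximation is rough: 119 × 0.057 is about 7 open-arm events by 3 years.

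**The case against.** The strongest defence is that the stated objective concerns low rectal cancer as a whole. An overall test controls error for that claim, and whether to claim by stage is partly a choice of estimand. That stands. A reader might infer from the 28% that the type I error is inflated about tenfold. It is not: with a true overall deficit of 6.29 points, the overall null hypothesis is false. The 28% is the chance of a correct overall claim that would mislead if applied to stage II/III.

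A reader might also infer that the test would pass with stage II/III observed 10 points worse. It would not. With no loss at one-sided 2.5%, the observed overall deficit must be below 10 − 1.96 × 2.71 = 4.7 points (4.1 with 20% loss). A 10-point stage II/III deficit with stage I equal gives 6.3 and fails. Even at one-sided 5% with no loss the limit is 5.5.

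Nor do the documents rule out an analysis by stage. They are silent: the noninferiority criteria are not spelled out, and the XXX row in Table 9 could hold stage. But a stage covariate or stratified model still yields one common treatment effect, so it would not supply the missing result.

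Finally, the overall analysis is not underpowered; its power exceeds the stated 80%. The mismatch is in what the 80% refers to.

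**Conclusion.** The point holds as a gap between sizing and analysis, and should be corrected. The 80% belongs to two stage-specific tests; the analysis actually listed has about 93–97% power if the arms are equal. Nothing in the DFS plan would reveal a true 10-point deficit confined to stage II/III, and an overall claim would then succeed with probability 28% (no loss) or 23% (20% loss) at one-sided 2.5%.

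That figure rests on stage I being exactly equal, the planned 37% stage I share and a risk-difference rule. The working shows how far it moves: down to about 9% with a worse stage I or a smaller stage I share, up to 42% with a 50% share. The plan sets no cap on stage mix, so 37% is only the planned value. The documents support neither a finding of type I error inflation nor one of inadequate overall power.

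**What to change.** In SAP 8.3.3:

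1. Add 3-year DFS for stage I and for stage II/III, as sized: Kaplan-Meier estimates and curves, the difference with a two-sided 95% confidence interval against −10 points, and a stage-by-treatment interaction. Add matching rows to Tables 7 and 8.
2. Keep the overall test first, stratified by stage. Then test stage II/III, then stage I, in fixed order, each at one-sided 2.5%. State that noninferiority is claimed for a stage only if its own lower limit is above −10 points.
3. In SAP 8.1, restate power separately: overall about 93–97%; stage II/III about 77–79% with no loss and 67–70% with 20% loss; stage I about 79% (log-rank) or 97% (risk difference) with no loss, and about 70% or 93% with 20% loss.

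**Cost.** A few more tables and a stated testing order. No patients or data are added: stage is already recorded, and protocol section 12 has the plan finalized before database lock. The overall claim gives up no alpha. A stage II/III claim has less power than the overall one, and success in both stages has about 0.790 × 0.793 = 63% power (log-rank, no loss). The rule also brings the difference in points, the scale of the stated margin, alongside the hazard ratio. It keeps 10 points in stage I as sized, although that corresponds to HR 2.91 there against 1.50 in stage II/III; reporting both scales would let readers see this.
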